### Data analysis

2.8

All data will be entered into IBM Statistical Packages for Social Sciences (SPSS) version 23.0. Intention-to-treat (ITT) method will be used; all the participants recruited at baseline will be included in the outcome analysis. Using ITT, missing data will be replaced with last observation carried forward. Socio-demography and health profile of the participants will be analyzed descriptively and reported as frequencies (percentages) and mean (standard deviation) or median (inter-quartile range). The effects of the interventions will be analyzed using mixed model ANOVA and reported as main time, group and time-group interaction effects for each intervention outcome. Level of significance will be set as *P* < .05 for all results.

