Studies have shown that functional decline occurred in stroke survivors post-discharge from rehabilitation due to poor exercise adherence, lack of motivation, musculoskeletal issues and fatigue.^[7]^ Past studies that assessed the function of stroke survivors at 1 year or more post-discharge reported deterioration of gait speed and balance ability among the survivors at several months of discharge.^[8,9]^ Therefore, the continuity of rehabilitation at post-discharge episode is crucial to prevent functional deterioration in stroke survivors. There is a need to review the existing “usual practice” and develop a better approach. A few studies have shown that functional deterioration can be impeded with a rehabilitation or care intervention based at home.^[9]^ Home-based therapy (HBT) was able to cease the deterioration and improve the performance of activities of daily living (ADL) in stroke patients.^[10,11]^ Thus, HBT might be an alternative approach for stroke survivors who require long-term management. However, the overall effects of HBT on post-discharged stroke patients remain unknown due to scarcity of research on this population. Self-efficacy and emotional aspect of stroke survivors play an important role in determining quality of life in long term post-stroke,^[12]^ but no studies have evaluated the effectiveness of HBT with regards to these outcomes. Therefore, the purpose of this study is to determine the effectiveness of HBT in stroke survivors following discharge from rehabilitation in term of functional outcome (mobility and gait speed), self-efficacy and anxiety level. This study also aims to assess the feasibility of HBT plan on this population.

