### Interventions

2.4

The interventions in this study will be conducted for 12 weeks. HBT group will receive home-based exercise program consisting of 9 strengthening, walking, task-related and balance exercises, which aim to improve muscle strength, balance and gait ability. The exercises were designed based on a protocol reported in a previous study^[14]^ and using the frequency, intensity, time and type (FITT) principle.^[15]^ The total duration of the exercise program is between 45 to 60 minutes, depending on the participants ability. Participants will be instructed to perform the given exercises at a comfortable pace for 3 times per week, monitored or assisted by their caregivers. Training session will be provided to all participants and caregivers by the main researcher prior to implementing home-based sessions. Logbook will be given to all participants to document their home-based exercise sessions. The graphic and instructions for exercises in the logbook were adopted from an exercise website (https://www.physiotherapyexercises.com/). Once per 2 weeks telephone call will be attempted for each participant to monitor their exercise adherence and occurrence of any potential adverse effects related to exercise such as muscle soreness and cramps. Exercises will be progressed with regards to intensity for participants who report no adverse effects. Table 1 shows the home-based exercise program to be provided to participants in HBT group.

**Table 1 T1:** Home-based exercise program for HBT group.

Warm up exercise (stretching exercise)
• Head turn with over pressure
• Neck lateral flexor stretch
• Posterior shoulder stretch
• Trunk rotation
• Hamstring stretch in sitting
• Seated gluteal stretch
1. Sit to stand exercise – any one exercise from the list below according to participant's standing balance and lower limb muscle strength:
• Sit to stand with support
- participant with poor standing balance
• Sit to stand without support
- participant with fair/good standing balance and muscle strength 3/5
• Sit to stand in tandem position
- participant with good standing balance and muscle strength above 4/5
• Sit to stand on a low stool
- advance participant with good standing balance and muscle strength above 4/5
2. Stepping in different directions
3. Stepping up and down stairs or a block
4. Reach to target exercise – any one exercise from the list below according to participants standing balance:
• Stand and reach to targets

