1.Functional performanceTime up and go (TUG) test will be used to assess mobility level and falls risk. The cutoff point of high risk of fall for stroke survivor is >14 seconds.^[16]^ TUG was shown to have high test-retest reliability (ICC = 0.96) and excellent correlation with the comfortable gait speed test (r = −0.86), fast gait speed test (r = −0.91), ascending stair climbing test (r = 0.86), descending stair climbing test (r = 0.90) and 6-minute walk test (r = 0.92).^[17]^ Participants will be instructed to stand up from a standard chair and walk safely as quickly as possible for 3-meter, turn around and walk back to the chair and sit down. The timing begins at the instruction “Go” and stops when participants sit down on the chair.The 10-meter walk test (10mWT) will be used to assess walking speed among participants and determine the functional ambulatory classification of each participants. The participant will be instructed to walk along the 10-meter walkway and stop at the end point with comfortable speed. The middle of the 6-meter walkway will be timed as the participant walks. The test will be repeated with fast walking speed. The 10mWT has high test-retest reliability (ICC = 0.95–0.99) in stroke survivors.^[18]^2.Self-efficacy: The stroke self-efficacy questionnaire (SSEQ), a 13-item self-administered questionnaire which designed specifically for stroke survivors will be used to assess the level of self-efficacy among the study participants. SSEQ consists of two self-efficacy domains: activity (items 1 to 8) and self-management (items 9 to 13).^[19]^ Participants need to rate their confidence level on a 3-point scale, from 0 which indicates “not at all confident” to 3 which represents “very confident”. The total score of SSEQ will be calculated by summation of each item score. Higher score of SSEQ indicates higher self-efficacy level.^[19]^ SSEQ has good reliability, with Cronbach α coefficient value 0.90 and person separation index (PSI) > 0.80 for both activity and self-management domains.^[19]^3.Anxiety level: Hospital anxiety and depression scale (HADS)^[20]^ will be used to measure anxiety level of the patient. HADS is divided into an anxiety subscale (HADS-A) and a depression subscale (HADS-D), each subscale contains 7 questions and can be calculated separately. HADS-A will be used to assess the anxiety level among participants at baseline and post-trial. The cut-off score for anxiety using HADS-A is 8 and above, with specificity of 0.78 and a sensitivity of 0.9. Bjelland et al^[21]^ who reviewed HADS in 747 studies reported that HADS-A has good reliability value, indicated by Cronbach's α coefficient between 0.68 to 0.93.

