
### Assessment of outcomes

2.6

All participants will be assessed at baseline and at the end of week 12 of interventions by a therapist who is blinded to the group allocation and trained to conduct the standardized tests. To avoid recall bias, the recorded baseline assessment data will not be accessible to the blinded assessor during the post-trial assessment.

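### With outcomes measured only at baseline and week 12, last observation carried forward scores every participant without a week-12 assessment as exactly zero change, which biases the time-by-group estimate whenever those participants truly change

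*Protocol article*

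**What the plan says.** Section 2.6 (Assessment of outcomes) sets two measurement times: "All participants will be assessed at baseline and at the end of week 12 of interventions". Section 2.5 (Outcomes) repeats this for anxiety: "HADS-A will be used to assess the anxiety level among participants at baseline and post-trial". Between the visits there is only telephone contact: "Once per 2 weeks telephone call will be attempted for each participant to monitor their exercise adherence". The calls also ask about adverse effects, but no efficacy outcome is collected on them.

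Section 2.8 (Data analysis) commits to intention to treat, so that "all the participants recruited at baseline will be included in the outcome analysis". It then gives one missing-data rule: "Using ITT, missing data will be replaced with last observation carried forward". Results come from a mixed model ANOVA, "reported as main time, group and time-group interaction effects for each intervention outcome". No other missing-data method and no sensitivity analysis is named beside this rule.

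Two further statements bear on the point. The Introduction says "Studies have shown that functional decline occurred in stroke survivors post-discharge from rehabilitation". Section 2.9 (Ethics and dissemination) lets participants withdraw at any time without giving a reason, so missing week-12 data are foreseeable.

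**The concern.** With a single post-baseline visit there is nothing to carry forward except baseline. Every participant who misses week 12 therefore enters the analysis as a person who neither improved nor declined.

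The trial asks whether home-based therapy (HBT) changes the course after discharge compared with usual practice (UP). If the natural course is decline, zero change is a good outcome credited to people who were never reassessed. If the course is improvement, zero change hides a gain. Either way the time-by-group effect, on which the trial is sized, no longer estimates the difference in mean change between the randomised arms. The same rule governs every outcome. With 21 per arm, four losses are 4/21 = 19% of an arm, so a handful of withdrawals is enough to matter.

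**Working it through.** **Inputs from the protocol article.** Two assessment times (section 2.6); 21 per arm, alpha 0.05 and power 80% (section 2.7); carry-forward and analysis of everyone recruited (section 2.8).

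**Inputs not stated.** Dropout rate, size of decline, effect size and the correlation between the two measurements. All values used for these are assumptions.

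**The plan's own figure.** The total of 42 cannot be confirmed or refuted, because effect size f and correlation rho are missing. It is attainable: with noncentrality f² × N × m/(1 − rho) and m = 2 times, f = 0.20 and rho = 0.6 give 42. The zero-change result does not depend on this.

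**Step 1: the imputed value.** Missing week 12 := baseline, so change = baseline − baseline = 0. This is arithmetic and needs no assumption.

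**Step 2: the estimate.** With two arms and two times, the interaction test is the two-sample t test on change scores. Let muH and muU be the true mean changes (positive = better) and pH and pU the dropout fractions, with dropout at random. Then:

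- target: muH − muU
- expected contrast under the rule: (1 − pH) muH − (1 − pU) muU
- bias: pU muU − pH muH

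The bias vanishes without dropout, when those who drop out truly do not change, or when the two terms cancel (for example equal dropout with equal change in both arms).

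**Step 3: a true difference.** At 21 per arm and change SD 1, the difference with 80% power is 0.886 SD. Take muH = 0 and muU = −0.886. Power is from simulation with 40,000 runs; observed data means only participants with a week-12 value.

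| Dropout HBT / UP | Expected contrast under the rule | Power, rule | Power, observed data |
|---|---|---|---|
| 10% / 10% | 0.90 × 0.886 = 0.80 | 74% | 75% |
| 20% / 20% | 0.80 × 0.886 = 0.71 | 68% | 70% |
| 30% / 30% | 0.70 × 0.886 = 0.62 | 61% | 63% |
| 10% / 30% | 0.70 × 0.886 = 0.62 | 55% | 69% |
| 30% / 10% | 0.90 × 0.886 = 0.80 | 79% | 69% |

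The observed-data estimate stays at about 0.89 throughout, as it should under random dropout.

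**Step 4: no true difference.** Both arms decline equally and HBT loses more patients.

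| Decline in both arms | Dropout HBT / UP | Spurious HBT benefit | Type I error |
|---|---|---|---|
| 0.8 SD | 20% / 10% | 0.8 × (0.20 − 0.10) = 0.08 SD | about 6% |
| 0.8 SD | 30% / 10% | 0.8 × (0.30 − 0.10) = 0.16 SD | about 9% |
| 0.3 SD | 30% / 10% | 0.3 × (0.30 − 0.10) = 0.06 SD | 5.5% |

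Observed-data type I error stays near 5%. The sign reverses if UP loses more patients, or if patients improve.

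**Step 5: the standard error.** Under the rule the variance of change in an arm is (1 − p) + p(1 − p)mu². At 20% dropout in both arms this is 0.80 for HBT and 0.80 + 0.16 × 0.886² = 0.926 for UP, so SE = √((0.80 + 0.926)/21) = 0.287. The simulated sampling SD of the estimate agrees (0.287 to 0.288). With nobody missing, SE = √(2/21) = 0.309; with observed data at 20% dropout it is about √(2/16.8) = 0.345. The formula therefore describes the carry-forward estimator correctly. But the interval is narrower than with complete data, and it is centred on 0.71 instead of 0.886.

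**The case against.** Much of the opposing case stands, and it limits the claim.

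- **Power.** A reader might infer that the rule causes the fall from 80% to 74%, 68% or 61% at equal dropout. It does not: observed data give 75%, 70% and 63%, so nearly all the loss comes from the missing patients. A clear power cost appears when UP, the declining arm, loses more (55% against 69%). In the reverse case the rule has the higher power (79% against 69%), around a biased estimate.
- **Standard errors.** A reader might infer that imputed zeros make the standard errors wrong. Step 5 shows that they match the estimator's sampling variation. The fault is the value on which the interval is centred.
- **Type I error.** The 9% needs a 0.8 SD decline within 12 weeks and threefold dropout in one arm. Milder settings stay at 5.5% to 6%.
- **Premise of decline.** A reader might infer that the rule necessarily flatters whichever arm loses more patients, because the trial presumes decline. The Introduction reports deterioration of gait speed and balance in studies that assessed survivors a year or more after discharge. It does not establish decline at 12 weeks, or any worsening of self-efficacy or anxiety. The Discussion itself says further improvement may be possible. The direction of bias is therefore open.

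Two defences fail. The rule is not reliably conservative, as step 4 shows. Nor does intention to treat require it: that principle fixes who is analysed and in which arm, not that a missing value be filled with baseline. Nor is this a detail left to an unseen analysis plan, since the article names the method.

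**Conclusion.** The point holds. The zero-change result is certain from sections 2.6 and 2.8 taken together, and nothing else in the document repairs it. Bias in the time-by-group estimate follows whenever participants without week-12 data truly change, apart from the cancelling cases in step 2.

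Its size is conditional on dropout and decline that the document does not give. On the illustrations, a true 0.886 SD effect is reported as 0.80 to 0.62 SD, and a null effect as a spurious 0.06 to 0.16 SD with type I error of 5.5% to about 9%. If dropout is low, or if those lost do not change, the harm is small or nil. The figures assume random dropout, a change SD of 1 and 21 per arm. The documents do not support a claim that the result will favour HBT, that power is lost mainly through the rule, or that the standard error formula is at fault.

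**What to change.** In section 2.8, delete the carry-forward sentence and keep the commitment to analyse all randomised participants. Suggested replacement: baseline and week-12 values are analysed as repeated outcomes in a likelihood-based linear mixed model (SPSS MIXED, REML) with group, time and their interaction, using all available data without imputation. This is valid if data are missing at random.

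Add two short commitments:

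- The week-12 assessment will be sought from every participant, including those who stop exercising, unless consent is withdrawn.
- One delta-adjusted sensitivity analysis will assume that participants without week-12 data declined, because the missing-at-random assumption cannot be checked.

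Multiple imputation within each arm from several predictors is not advised as the main alternative, since it may be unstable at 21 per arm.

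The cost is a few sentences and slightly more analysis in software already chosen, with no new participants. Confidence intervals will widen when data are missing (in the 20% example, a standard error of about 0.345 instead of 0.287), which reflects the information actually lost. The change should be made before unblinded data are analysed.

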### Participants allocation

2.3

Stroke survivors will be randomized into either HBT (experimental group) or UP (control group) using stratified randomization method, with the use of microsoft-excel 2016 software by an independent researcher. Stratification variables are age, consisting of adult (18–59 years), young-old (60–74 years) and old-old (75–85 years), and disability level, namely 1 (no significant disability), 2 (slight disability) and 3 (moderate disability). Using the software, a random number column of subjects will be generated, and by using the sort function, recruited subjects will be stratified according to the sequence of age, disability level and random number. Subjects are then alternately allocated into each trial arm according to their age and disability level categories. Therefore, both the HBT and UP trial arm will consist of subjects with the different age and disability levels.

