### Sample size

2.7

GPower software version 3.0.10 was used to estimate required sample size for this study. This study used mixed model analysis of variance (ANOVA) to analyze time, group and interaction effects of the interventions. Therefore F-test (ANOVA repeated measure, within-between interactions) were chosen. The study power was set at 80% and alpha value set at 0.05. Based on these, a minimum sample of 42 subjects is required, i.e., 21 participants in each arm.

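### The time and group main effects are reported as intervention effects beside the interaction; only the interaction compares HBT with UP, and a baseline-adjusted difference would be more precise

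*Protocol article*

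**What the plan says.** Section 2.8 (Data analysis) names a mixed model ANOVA and says how the effects of the interventions will be presented: "reported as main time, group and time-group interaction effects for each intervention outcome". The same section applies the .05 significance level "for all results". No term is singled out as the test of effectiveness, and no covariate is named.

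Section 2.7 (Sample size) uses the same language: "This study used mixed model analysis of variance (ANOVA) to analyze time, group and interaction effects of the interventions". The calculation itself is narrower: "Therefore F-test (ANOVA repeated measure, within-between interactions) were chosen". It continues: "The study power was set at 80% and alpha value set at 0.05", and concludes that "a minimum sample of 42 subjects is required, i.e., 21 participants in each arm".

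Three other places matter. The Abstract states a between-arm aim, HBT compared with UP. Section 2.6 has two assessments, baseline and the end of week 12. Section 2.3 stratifies the randomisation by age and disability level, three categories each.

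**The concern.** Three tests per outcome carry the label of intervention effect, but with one pre-treatment and one post-treatment visit two of them do not estimate what HBT adds to UP.

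- **Time main effect.** This is the average change over all patients, whichever arm they are in. Section 2.4 has the UP arm exercising, keeping a logbook and receiving fortnightly calls, and the Discussion says many patients are discharged while they could still improve. Change in both arms is therefore plausible even if HBT adds nothing. A significant time effect could be reported as the interventions working.
- **Group main effect.** This averages the week-12 difference with the baseline difference, whose expectation is zero under randomisation. It is diluted by half and carries any chance baseline imbalance. A non-significant result could be taken to mean that HBT adds nothing.

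The interaction is the right kind of contrast, but with two visits it only subtracts baseline. Regressing on baseline uses the same data more efficiently, which matters in a trial of 42.

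**Working it through.** **Inputs from the article.** N = 42, 21 per arm; alpha 0.05; 80% power for the within-between interaction; two visits (2.6, 2.7).

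**Assumed.** The article does not give the effect size f or the baseline-to-week-12 correlation rho. I show rho = 0.3 to 0.8, with unit SD at both visits and no dropout.

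**The plan's own figure.** For two arms and two visits, the noncentrality of the interaction test is lambda = f² × N × 2 / (1 − rho), with 1 and N − 2 df. The figure of 42 can be neither confirmed nor refuted without f and rho, but it is attainable: f = 0.225 with rho = 0.5 gives 42, and f = 0.20 with rho = 0.6 gives 42. (f = 0.25 with rho = 0.5 would give 34.)

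**What each term estimates.** Let d be the true week-12 difference in SD units, with equal expected baselines.

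- Interaction: difference in mean change = d. Variance of a change = 2(1 − rho). With two visits its F statistic is the square of the t-test on change.
- Group main effect: difference in the two-visit average = (0 + d)/2 = d/2. Variance of that average = (1 + rho)/2.
- Time main effect: mean change over both arms, whatever d is.
- ANCOVA on week 12 with baseline as covariate: d, with residual variance 1 − rho².

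**Noncentralities.** N/4 = 10.5 throughout.

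- Interaction: 10.5 d² / [2(1 − rho)]
- Group: 10.5 (d/2)² / [(1 + rho)/2], which is (1 − rho)/(1 + rho) times the interaction value
- ANCOVA: 10.5 d² / (1 − rho²), which is 2/(1 + rho) times the interaction value

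Example at rho = 0.5, where 80% interaction power needs d = 0.886 (d² = 0.785):

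- Interaction: 10.5 × 0.785 / 1 = 8.24
- Group: 10.5 × 0.196 / 0.75 = 2.75
- ANCOVA: 10.5 × 0.785 / 0.75 = 10.99

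Power from the noncentral F (40 error df; 39 for ANCOVA):

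| rho | d for 80% | Interaction | Group main effect | ANCOVA | ANCOVA variance ÷ change variance, (1 + rho)/2 |
|---|---|---|---|---|---|
| 0.3 | 1.048 | 80% | 54% | 93% | 0.65 |
| 0.5 | 0.886 | 80% | 37% | 90% | 0.75 |
| 0.7 | 0.686 | 80% | 22% | 86% | 0.85 |
| 0.8 | 0.560 | 80% | 15% | 84% | 0.90 |

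**Simulation check** (40,000 trials, 21 per arm, rho 0.5 and 0.7):

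- With a true effect of 0.886 SD or 0.686 SD, the group term averaged 0.441 and 0.343, half of each.
- With both arms improving by an assumed 0.5 SD and no effect of HBT, the time effect was significant in 89% (rho 0.5) and 98% (rho 0.7) of trials.
- With no treatment effect, the interaction or the group term was significant in just under 10% of trials per outcome. With no change over time either, at least one of the three terms was significant in about 14%.

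**Cost of further covariates.** Age and disability as three-level factors use 2 + 2 = 4 df. Cutting the ANCOVA error df from 39 to 35 lowers its power by about 0.2 percentage points in every row, before any gain they bring. That gain cannot be computed from the article.

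**The case against.** The strongest reply is that the right test is already there. The interaction is planned, reported and the only term on which the trial was sized, and the stated aim is plainly between-arm. Nothing in 2.8 says that a time or group effect will establish effectiveness, so the harm depends on misreading, and low power for a term nobody sized is unsurprising. This stands as mitigation. It does not remove the fault: 2.7 and 2.8 both call all three terms effects of the interventions, and 2.8 does not carry the sizing choice into the analysis. A fuller analysis plan could say which term decides, but it cannot turn a pooled change over time into an effect of HBT.

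A second reply is that change scores and ANCOVA are both valid under randomisation, and that the gain depends on an unknown correlation. That is also true. The gain falls to 84% against 80% at rho = 0.8 and to about 82% at rho = 0.9. The test-retest coefficients in 2.5 (0.96 for the timed up and go; 0.95 to 0.99 for the 10-metre walk) measure reliability, not correlation over 12 weeks, so they do not settle rho.

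A reader might go further and infer that the analysis ignores baseline, or is wrong because it leaves out the stratification factors. The article supports neither. Baseline is one of the two repeated measurements and the interaction subtracts it, so the cost is precision and not bias. On age and disability level the article is merely silent. A condensed article may leave covariates to a full plan, and omitting stratification factors usually makes the test conservative rather than invalid. Hospital is not a stratification factor in 2.3, so its absence from the model is no fault.

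**Conclusion.** The point holds as one of labelling and efficiency. Two of the three quantities presented as intervention effects are not estimates of the HBT-versus-UP effect: one contains no between-arm information, and the other is half the effect with 15% to 37% power (rho 0.8 to 0.5) where the interaction has 80%. Treating either the group term or the interaction as evidence roughly doubles the 5% false-positive rate per outcome. The planned interaction remains a valid, unbiased test.

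Using baseline as a covariate would reduce the variance to (1 + rho)/2 of the change-score variance, a gain of about 4 to 10 points of power for rho 0.8 to 0.5. That the time effect lacks between-arm information and that the group effect is halved follow from the two-visit design. The power figures rest on the assumed correlations, equal SDs at both visits and complete data. This should be changed before analysis, but it does not invalidate the trial.

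**What to change.** In 2.8, name one between-arm contrast as the treatment effect for each outcome. The preferred choice is the baseline-adjusted week-12 mean difference, HBT minus UP, with its 95% CI, from ANCOVA or a mixed model with baseline means constrained equal. If the mixed ANOVA is kept, the time-by-group interaction should be that contrast, reported as the difference in mean change with its 95% CI. Either way, present the time and group main effects as descriptive only, and align the wording of 2.7.

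It is advisable to state whether age and disability level enter the model. Including them costs a few degrees of freedom; hospital need not be required.

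The cost is a few sentences. Data, software and sample size stay as they are.

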**Methods::**

This is an assessor-blinded randomized control trial comparing 2 types of intervention which are HBT (experimental group) and usual practice (UP) (control group). Based on sample size calculation using GPower, a total number of 42 participants will be recruited and allocated into either the HBT or the UP group. Participants in HBT group will receive a set of structured exercise therapy consisting of progressive strengthening, balance and task-related exercises. While participants in UP group will receive a usual “intervention” practised by rehabilitation professional prior to discharging stroke patients from their care. Both groups are advised to perform the given interventions for 3 times per week for 12 weeks under the supervision of their caregiver. Outcomes of interventions will be measured using timed up and go test (for mobility), ten-meter walk test (for gait speed), stroke self-efficacy questionnaire (for self-efficacy) and hospital anxiety and depression scale (for anxiety level). All data will be analyzed using descriptive and inferential statistics.

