### Outcomes

2.5

Feasibility of both interventions will be assessed with regards to patients acceptance and adherence, and the occurrence of adverse effect.

1.Stroke survivors acceptance will be collected during post-trial assessment with question of “What do you think about this home-based therapy?”. Response from the survivors will be categorized into positive and negative responses and analysed descriptively.2.Adherence rate will be reported in term of percentages of practice (number of sessions performed out of the total sessions required i.e., 36 sessions). Number of practice sessions performed will be obtained from participants logbook.3.Occurrence of adverse effects related to exercise such as muscle soreness, cramps and muscle strain will be monitored through telephone call (once every 2 weeks) and during post-trial assessment.

The intended outcomes of the interventions in this study are:

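### No outcome is named primary while P < .05 applies to every result: if any one significant time-by-group interaction may count as effectiveness, the false-positive rate is about 14–18%, roughly three times 5%

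*Protocol article*

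**What the plan says.** Section 2.5 (Outcomes) introduces the effect measures with "The intended outcomes of the interventions in this study are" and lists functional performance (TUG and 10-metre walk test, 10mWT), self-efficacy (SSEQ) and anxiety (HADS-A), in no order of priority. The abstract gives the same four instruments: "Outcomes of interventions will be measured using timed up and go test (for mobility), ten-meter walk test (for gait speed", followed by SSEQ and HADS. For the 10mWT, section 2.5 adds: "The test will be repeated with fast walking speed". It does not say whether both speeds are analysed as outcomes.

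Section 2.6 sets two time points: "All participants will be assessed at baseline and at the end of week 12 of interventions".

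Section 2.7 (Sample size) chooses the within-between interaction F-test and states: "The study power was set at 80% and alpha value set at 0.05". The result is 42 participants, 21 per arm. No outcome is attached to the calculation.

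Section 2.8 (Data analysis) analyses each outcome by mixed-model ANOVA, "reported as main time, group and time-group interaction effects for each intervention outcome", and then fixes the threshold: "Level of significance will be set as *P* < .05 for all results".

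**The concern.** The 5% error rate in section 2.7 belongs to one test. The plan runs that test on four or five measures and gives each the same unadjusted threshold. Nothing in the text says which measure decides whether HBT is effective, or what happens if the measures disagree. The outcome that carries the conclusion could then be chosen after the results are known, and a reader could not tell a positive trial from one chance finding among several.

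This is more than detail left to an analysis plan. The article itself states the threshold for all results, so a later plan that adjusted for multiplicity would have to depart from it. It also presents a sample size without the outcome that the sample size is meant to serve.

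**Working it through.** **Inputs from the article.** Alpha is 0.05 per test (section 2.8). There are 21 per arm (section 2.7) and two time points (section 2.6). There are four measures, or five if both walking speeds are analysed (section 2.5). Section 2.5 also cites, for TUG, "excellent correlation with the comfortable gait speed test (r = −0.86), fast gait speed test (r = −0.91".

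**Assumptions.** The two gait speeds correlate 0.9. All other between-outcome correlations are 0, 0.3 or 0.5 in size. Baseline and week 12 correlate 0.5. The cited correlations, which are between scores, are taken to apply to changes as well.

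**1. The plan's own figure.** Section 2.7 gives no effect size or correlation, so 42 can be neither confirmed nor refuted. It can be solved backwards. For two groups and two time points the interaction F-test has 1 and N − 2 degrees of freedom and noncentrality λ = f²·N·2/(1 − ρ). With N = 42 and ρ = 0.5, 80% power needs f = 0.2215:

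λ = 0.2215² × 42 × 2 / 0.5 ≈ 8.24

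This equals a standardised between-arm difference in change of 0.886, since 0.886² × 21/2 ≈ 8.24. The 80% applies to one such test.

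**2. Ceiling under independence.** The familywise rate is 1 − 0.95^k.
- Interaction only: k = 4 gives 1 − 0.8145 = 18.5%; k = 5 gives 1 − 0.7738 = 22.6%.
- Interaction plus group main effect: k = 8 gives 33.7%; k = 10 gives 40.1%.

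The TUG and gait correlations cited in the article rule out independence, so these are upper bounds.

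**3. With correlation.** 40,000 null trials were simulated for each setting, with 21 per arm. The table gives the probability of at least one P < .05. The four-measure case uses TUG, comfortable speed, SSEQ and HADS-A.

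| Other correlations (assumed) | Interaction, 4 measures | Interaction, 5 measures | Interaction or group, 4 measures | Interaction or group, 5 measures |
|---|---|---|---|---|
| 0 | 16.6% | 17.9% | 30.2% | 32.0% |
| 0.3 | 15.8% | 16.9% | 29.1% | 30.9% |
| 0.5 | 14.5% | 15.7% | 27.3% | 28.6% |

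For the interaction alone this is 14.5/5 = 2.9 to 17.9/5 = 3.6 times the nominal rate. At assumed correlations of 0.3 to 0.5, counting the group effect as well gives 27.3/5 = 5.5 to 30.9/5 = 6.2 times.

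**4. Direction.** These are two-sided rates. False positives favouring HBT are about half. For four independent tests, 1 − 0.975⁴ = 9.6%, against 2.5% for one test. The multiple is almost the same (3.9 against 3.7).

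**5. Options for control.** One primary outcome judged on the interaction gives 5%, with N = 42 and 80% power unchanged. A Bonferroni split over four outcomes (0.05/4 = 0.0125) lowers power per outcome at N = 42 to 60.3% and needs 62 participants for 80%. Over five (0.01) the figures are 57.0% and 64. These use the back-solved effect from step 1.

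**The case against.** **Separate questions.** The aim names mobility and gait speed, self-efficacy and anxiety. If each is concluded on separately, each keeps its own 5% rate. That is fair: the inflation arises only when any one positive result is turned into a general claim of effectiveness. The article states no such rule, but nothing in it prevents one, and its aim and discussion speak of the effectiveness of HBT as a whole.

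**The contrast is already identified.** Section 2.7 sizes the trial on the interaction, which points to it as the key test. This stands, and it is why the main figure here is about threefold. The sixfold figure needs the group main effect to be a second route to a claim. Section 2.8 reports that effect beside the interaction without saying which decides. With only baseline and week 12 in the model, the group effect averages in pre-treatment values and is a poor measure of treatment.

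**Unseen documents.** A full protocol, analysis plan or the registration may name a primary outcome. The point is therefore established for the article only.

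**Stronger readings that the text does not support.** A reader might multiply five measures by three ANOVA effects and conclude that any of 15 tests could show effectiveness, with an error rate of 1 − 0.95¹⁵ = 54%. Five of those tests are time main effects, which pool both arms and say nothing about HBT versus UP, while the stated question is comparative. A reader might also take 22.6% as the size of the problem. That figure assumes independence, which the cited correlations contradict, and five analysed measures, which the text does not settle.

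**Conclusion.** The point holds for the article as written. It ranks no outcome, ties its single powered test to none, and applies an unadjusted threshold to all results. If any one significant interaction may be presented as effectiveness, the false-positive rate is about 14–18%, roughly three times the stated 5%. It is about 27–31% only if the group main effect is accepted as well. These figures rest on the cited TUG and gait correlations and on assumed moderate correlations elsewhere; zero correlation elsewhere gives the top of the first range and 32% for the second. The point does not show that N = 42 is wrong, nor that the investigators intend to select an outcome after the fact.

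**What to change.** Before unblinding:

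- In section 2.5, name one primary outcome. The choice is the investigators' (TUG is one example) and should be consistent with the registration. State which 10mWT speed is analysed, or that both are.
- In section 2.7, tie the calculation to that outcome.
- In section 2.8, state that effectiveness is judged on the HBT versus UP time-by-group contrast for the primary outcome at two-sided 0.05. Label the other outcomes secondary, and either apply Holm's adjustment across them or report estimates with 95% confidence intervals and no confirmatory claim. Replace the blanket significance rule accordingly, and say that time and group main effects are descriptive.

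The cost is wording in three sections. N = 42 does not change. The price is that the other outcomes lose confirmatory status. If the investigators want several confirmatory outcomes instead, alpha must be shared, with the loss of power or larger sample shown in step 5 of the working.
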